### Objectives and hypotheses

We believe that the implementation of transdiagnostic therapy at the primary level using a stepped-care model would save costs and reduce waiting lists. Mild to moderate cases could be treated in primary care and severe ones could be referred to specialized care for combined and more intensive therapies.

The proposed trial aims to compare, in terms of cost-effectiveness and cost-utility, a brief, transdiagnostic CBT in two different formats, individual and group, with the treatment ordinarily administered in primary care (treatment as usual [TAU]) for mild to moderate EDs (i.e., depressive, anxiety, and somatoform disorders). We expect that:

#### Hypothesis 1

Individual treatment will be generally as effective as group treatment in reducing emotional symptoms and cognitive-emotional regulation biases (i.e., both will show similar post-intervention size effects).

#### Hypothesis 2

The TAU will be the least effective (i.e., with significantly lower post-intervention size effects).

#### Hypothesis 3

The group therapy will return the best results in terms of cost-effectiveness and cost-utility.

#### Hypothesis 4

The TAU will have the least cost-effectiveness and cost-utility ratios.

#### Hypothesis 5

The same results will be found across the follow-up assessments (6 and 12 months after intervention).

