### Interventions

#### Group brief transdiagnostic cognitive-behavioural therapy (group tCBT)

It was developed by Cano-Vindel [43] and is based on the Unified Protocol for the Transdiagnostic Treatment of Emotional Disorders (UP) [44] and the IAPT programme [21]. It consists of seven 90-min sessions over 12–16 weeks and is conducted by a non-assessor clinical psychologist (hereafter the therapist), with 8–10 participants per group. Sessions are weekly or biweekly, and reduce in frequency as the intervention progresses; they are described below. (See Table 1 for the timeline.) The activities and homework are supported with materials such as theory documents, a CD for progressive muscle relaxation, self-recording sheets, and a therapy web. For more information, see González-Blanch et al. [43].

**Table 1 Tab1:** Group tCBT’s session timeline [43]

Therapy contents	Sessions						
	1	2	3	4	5	6	7
1. Psychoeducation	**×**	**×**					
2. Relaxation	**×**	**×**					
3. Cognitive restructuring			**×**	**×**	**×**	**×**	**×**
4. Behavioural techniques				**×**	**×**	**×**	**×**
5. Relapse prevention							**×**

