### Sample size

We used effect sizes from the previous literature to determine the sample size. Corpas et al.’s primary care RCT [41] compared both group and individual brief tCBT with TAU for emotional disorders and found low to medium effect sizes for all outcomes. Individual effects were larger (Cohen’s *d* ranged from .54 to .74) than group effects (.4 to .63) when compared with TAU; however, there was no significant difference between both transdiagnostic formats, with (very) low effect sizes (.06 to .27). Another primary RCT by Corpas et al. [36] compared tCBT with TAU and found medium to large effect sizes (from .39 for depression to .81 for panic symptoms). Finally, the PsicAP study compared the group tCBT used herein to TAU in primary care. Intention-to-treat analyses showed low to medium effect sizes over time for depression (Morris’ *d* ranged from .36 to .58), anxiety (.38 to .65), and somatizations (.31 to .4). Subsequently, we decided to assume a medium effect size of .6 (Cohen’s *d*).

Since software to determine sample sizes for linear mixed model analyses was not available, we used the *f* index of G*Power [52]. We assumed an effect size of .3 (the equivalent *f* value); a statistical power (1 - *β*) of .8; and a significance level (*α*) of .05, obtaining a required sample size of 111. However, to control withdrawals and take into account the abandonment rates in other similar trials [36, 41], we assumed a dropout rate of 15%, which brought the required sample size to 128.

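### The sample size converts d = .6 to f = .3 with a two-group rule but uses it in a three-arm test, so on the stated method 111 gives about 75% power, not 80%

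*Protocol article*

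**What the plan says.** The Sample size section reviews earlier trials and concludes: "we decided to assume a medium effect size of .6" (Cohen's d). Because no software for linear mixed models was available, the authors used the f index of G*Power: "We assumed an effect size of .3", which they call the equivalent value of f, with power "of .8; and a significance level" "of .05, obtaining a required sample size of 111". A 15% dropout allowance brings this to 128. The G*Power test is not named.

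Trial design fixes three parallel arms at 1:1:1 with four measurement times. Hypothesis 1 expects the two therapy formats to be similar. Hypothesis 2 reads: "The TAU will be the least effective (i.e., with significantly lower post-intervention size effects". Under Statistical methods, outcomes are analysed with linear mixed models, and therapeutic success is judged against the controls at p ≤ .05. Group therapy is delivered "with 8–10 participants per group"; the sample-size text makes no allowance for this.

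**The concern.** Cohen's f is the standard deviation of the arm means divided by the within-arm standard deviation. For two equal groups that is exactly d/2, so d = .6 gives f = .3. For three groups it depends on where the third mean lies, and it is always below d/2 when d is the largest difference. If a two-group f was entered in a three-group test, the calculation assumes a larger effect than the d = .6 the text adopts.

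An omnibus test also does not match the claims. Hypothesis 2 and the success criterion concern each therapy arm against TAU, and a single contrast uses only two thirds of the sample. What is at stake is how the result is read: a non-significant comparison with TAU would be weighed against an 80% power that the stated calculation does not deliver at d = .6.

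**Working it through.** **Inputs from the article.** d = .6, f = .3, power .80, alpha .05, 15% dropout, 111 and 128 (Sample size); three arms at 1:1:1 (Trial design); therapy groups of 8–10 (Group tCBT). Two-sided testing is assumed for pairwise contrasts, since sidedness is not stated.

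**1. Reproduce 111.** One-way omnibus F test, k = 3, noncentrality λ = N·f², degrees of freedom 2 and N − 3. With f = .30 and N = 111, λ = 111 × .09 = 9.99 and power = .803. In equal arms, 111 (37 per arm) is the smallest N that reaches .80. Other settings do not match: two groups at f = .3 give 90; a between-arm repeated-measures test (four times, correlation .5) gives 72; a within-between interaction gives 24.

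**2. The f that d = .6 implies with three equal arms.**
- Means 0, .6, .6 (Hypotheses 1 and 2 together): f = .6 × √2/3 = .283, the maximum.
- Means 0, .3, .6 (evenly spaced): f = √[(.09 + 0 + .09)/3] = .245.

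No arrangement reaches .30. Conversely, f = .30 needs d = .30 × 3/√2 = .636 in the first pattern and .735 in the second.

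**3. Omnibus power at d = .6 with 111 completers.**

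| Means | f | λ | Power | N for 80%, equal arms |
|---|---|---|---|---|
| 0, .6, .6 | .283 | 8.88 | .752 | 126 |
| 0, .3, .6 | .245 | 6.66 | .619 | 165 |

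**4. Each therapy arm against TAU.** Noncentral t, 37 per arm, two-sided .05: noncentrality = .6 × √(37/2) = 2.58 on 72 df, power .721. Reaching 80% takes 45 per arm, or 135 in total, or a true d of .66.

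**5. Completers actually expected.** 128 × .85 = 108.8, about 109 (36.3 per arm). Omnibus power for 0, .6, .6 is .744, with 80% at d = .64. Pairwise power is .713.

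**6. Baseline adjustment (correlation ρ assumed; not in the article).** Adjusting for baseline divides the residual SD by replacing it with √(1 − ρ²) times its value, so d becomes .6/√(1 − ρ²). Pairwise power at 37 per arm:

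| ρ | 0 | .3 | .4 | .5 | .6 |
|---|---|---|---|---|---|
| Power | .721 | .761 | .793 | .836 | .889 |

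It passes .80 a little above ρ = .4.

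**7. Therapy groups (ICC assumed; not in the article).** The design effect 1 + (m − 1) × ICC is applied to the group arm only. For m = 8 to 10 and ICC .01 to .10 it runs from 1.07 to 1.90, and unadjusted group-versus-TAU power at d = .6 falls from .71 to .56. With ρ = .5 it is .80 to .82 at ICC .01 to .02, and about .76 to .77 at ICC .05.

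**The case against.** The best defence is that the calculation is a declared proxy. The authors say they lacked software for mixed models, and the f-index calculation credits no correlation between measurements. The planned model could recover the shortfall: step 6 shows each pairwise comparison reaching 80% with a modest baseline correlation. A pooled contrast of both therapy arms against TAU (74 against 37) would have 84% at d = .6, and a one-sided .05 pairwise test 82%. This stands as far as it goes. A reader might infer that the trial lacks 80% power for every stated hypothesis, and the documents do not support that. But the article states no correlation, no pooled contrast and no one-sided test, so none of these is the justification it offers.

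A reader might also infer that d = .6 is out of line with the cited evidence. It is not clearly so. The group-versus-TAU figures run from .31 to .81 once all three trials are counted, including the .39 to .81 of the second primary care trial, whose treatment the Background describes as a group intervention. Individual therapy has .54 to .74. Some of these figures are Morris' d over time, so the metrics are mixed.

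Finally, a reader might infer that the analysis will ignore therapy groups and inflate the type I error. The article names linear mixed models without giving their random effects, a detail that may sit in a fuller plan not shown. Only the absence of an allowance in the sample-size calculation is established. Likewise, the omnibus test is inferred from the number 111; the Statistical methods section does not prescribe it as the analysis.

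**Conclusion.** The conversion is wrong for three arms, and the stated 80% does not follow from the article's own inputs. At d = .6 and 111 completers, the method used gives about 75% omnibus power at best, 62% if the arms are evenly spaced, and about 72% for each therapy arm against TAU (two-sided .05). The omnibus figures need no outside assumption beyond identifying the test, which rests on the exact match at 111.

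The power of the planned mixed model is not determined. A baseline correlation a little above .4 would bring each comparison to 80%; clustering in the group arm would take some of that back. The gap is moderate: f = .30 corresponds to d of about .64 rather than .6 under the most favourable pattern.

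**What to change.** Keep the enrolment and restate the power, for example:

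> With 128 enrolled and 15% dropout, about 109 completers give about 74% power for the omnibus test if both therapy arms differ from TAU by d = .6 (80% at d = .64), and about 71% for each comparison with TAU, before baseline adjustment and clustering.

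Tie the calculation to the two therapy-versus-TAU contrasts on which Hypothesis 2 and the success criterion rest. If baseline adjustment is to be credited, state the assumed correlation and its source, and give the power over a range of ICCs for the group arm. If the full analysis plan does not already do so, include a random effect for therapy group in the group arm only.

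The cost is one reworded paragraph and possibly one extra variance term. The downside is a less favourable stated power and slightly wider intervals for the group arm.

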### Trial design

This intervention trial has a randomized, controlled, multicentre, and single-blinded design with 3 parallel groups, a 1:1:1 allocation ratio, and 4 measurement times: pre-intervention, immediately after the intervention, and two follow-ups (at 6 and 12 months; see Fig. 1).

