## Discussion

This protocol tries to combine the strengths of the PsiBrief and the PsicAP projects. The large PsicAP project [34, 35] studied a brief group transdiagnostic intervention as a more cost-effective possibility for ED treatment in primary care; however, as has been noted, group therapy is less flexible (and less popular amongst patients) than individual therapy (which allows for stronger therapeutic relationships). Meanwhile, the PsiBrief project [40, 41], which introduced individual therapy, saw a high attrition rate, so follow-ups were not possible. Also, it did not include cost-benefit analyses. The proposed study will try to combine the best of each of these projects, comparing the cost-effectiveness and cost-utility of both group and individual transdiagnostic therapy with TAU in primary care.

Based on PsiBrief and PsicAP’s results, we hypothesize that our proposed experimental interventions will be equally effective in reducing emotional symptoms and improving emotion regulation strategies, and TAU will be the least effective. Since group therapy involves several patients with different symptoms, we hypothesize that it will have the best outcomes in terms of cost-effectiveness and cost-utility, and TAU the worst. Finally, we hypothesized that these results will be sustained in the follow-ups.

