Finally, this kind of trial risks a high dropout rate and missing data, especially at follow-ups. Unlike the IAPT programme, the proposed study will not take session-by-session measurements, because the number of instruments we are using would make it difficult. We hope, therefore, that the clinical psychologists will encourage participants to complete the measurements through regular telephone calls. Finally, due to the duration of the study, intervention and measurements might be affected by patients’ availability (holidays, medical appointments, and so on), but we will make an effort to ensure that timings are similar between groups.

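### The 15% dropout allowance multiplies by 1.15 where it should divide by 0.85, so 128 falls just short of leaving the required 111; the text should also say which assessment the 15% covers

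*Protocol article*

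**What the plan says.** The Trial design section describes "3 parallel groups, a 1:1:1 allocation ratio, and 4 measurement times"; the four times are baseline, post-intervention, 6 months and 12 months. The Sample size section works with the *f* index of G*Power. It states "We assumed an effect size of .3 (the equivalent *f* value"), "a statistical power (1 - *β*) of .8" and "a significance level (*α*) of .05", and reports a requirement of 111. It then refers to the abandonment rates of two similar trials (references 36 and 41) and concludes: "we assumed a dropout rate of 15%, which brought the required sample size to 128". It does not say which assessment the 15% or the .8 power refers to.

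Two later sections bear on the 15%. The Discussion says that the PsiBrief project, published as references 40 and 41, "saw a high attrition rate, so follow-ups were not possible". The Anticipated limitations section says that "this kind of trial risks a high dropout rate and missing data, especially at follow-ups".

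**The concern.** An allowance for dropout exists so that the number left after losses still meets the calculated requirement. If it is added as a percentage of the requirement instead of being taken out of the number enrolled, the result is always too small. Here the stated total does not deliver the plan's own target under the plan's own dropout rate, and a reader who checks the sentence will find that it does not hold.

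The second matter is one of support. Reference 41 is one of the two sources for the 15%, yet the Discussion places the same reference in a project that lost too many participants to carry out follow-ups. Hypothesis 5 concerns the 6- and 12-month assessments, and cost data are collected to 12 months after the intervention. A reader could therefore take the single 15% and the single .80 to hold at every visit, although the article itself expects heavier losses later.

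**Working it through.** **Inputs.** From Sample size: *f* = .30, α = .05, power .80, 111 before dropout, 15% dropout, 128 after dropout. From Trial design: three arms, 1:1:1. The type of test is not stated; a one-way omnibus F test is assumed because it reproduces the plan's figure.

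**Step 1: reproduce 111.** With k = 3 arms and total N, power = P(F′ > F crit), where F′ is noncentral F with k − 1 = 2 and N − 3 degrees of freedom and noncentrality λ = N f².

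- N = 110: λ = 110 × 0.09 = 9.90, power .7996
- N = 111: λ = 111 × 0.09 = 9.99, power .8035

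The smallest N that reaches .80 is 111, exactly as stated, and it divides equally into three arms of 37.

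**Step 2: reproduce 128.** 111 × (1 + 0.15) = 127.65, rounded up to 128. This is how the stated figure arises.

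**Step 3: the allowance that 15% dropout requires.** If N are enrolled and a fraction d is lost, N(1 − d) remain. Setting this to 111 gives N = 111 / (1 − 0.15) = 130.6, that is 131. The next multiple of three is 132. Check: 131 × 0.85 = 111.35 and 132 × 0.85 = 112.2, both at or above 111. By contrast, 128 × 0.85 = 108.8, about 2 short.

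**Step 4: what the shortfall costs.** Omnibus power at *f* = .30:

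- 108 remaining: .792
- 108.8 (the exact product): .795
- 109 remaining: .796

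The target case, 111 remaining, has .8035. The loss is about 0.8 to 1.2 percentage points.

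**Step 5: the dropout that 128 does tolerate.** 1 − 111/128 = 17/128 = .133, or 13.3%.

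**Step 6: the later visits, for illustration only.** The documents give no attrition percentage for either cited trial, so the loss rates here are assumptions. With 128 enrolled and the same F test:

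| Assumed loss | Remaining | Omnibus power |
|---|---|---|
| 15% (the plan's rate) | 108.8 | .795 |
| 20% | 102.4 | .77 |
| 30% | 89.6 | .71 |

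These values take no credit for baseline scores or for partial data in the mixed model.

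**The case against.** The strongest reply is that this is a rounding-scale matter. Three participants on 128 is 2.3%, power moves from .80 to about .79, and no design decision depends on it. That stands, and it is why the point is small. It does not make the sentence correct: the article states a rate, a requirement and a result, and the three do not agree.

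On the source of the 15%, a reader might infer that the Discussion contradicts the Sample size section, or that the trial lacks the 80% power it claims at 12 months. The documents do not support either inference. The 15% is credited jointly to references 36 and 41, and nothing is said about attrition in reference 36. The Discussion gives no percentage for the PsiBrief project and does not say when participants were lost, so a modest post-treatment loss followed by failed follow-up would fit both statements. Nor does the Sample size section claim 80% power at any named visit. Hypotheses 1 and 2 are worded on post-intervention effect sizes, and the success criterion under Analysis of clinical effectiveness is worded on post-intervention means, so post-treatment is the natural reading. Hypotheses 3 and 4 rest on bootstrapped cost ratios, which the F test does not describe.

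The plan also contains mitigations. Participants who leave treatment are still invited to complete questionnaires, telephone calls are planned to retain them, and linear mixed models use incomplete records. As an illustration, if baseline and outcome correlate at .3 to .6 (an assumption), a baseline-adjusted test with 90 participants would have power of about .75 to .89 at *f* = .30, against about .71 unadjusted. Separate dropout rates and power for each visit are detail that a condensed article may leave to the full protocol.

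**Conclusion.** The arithmetic point holds. Under the article's own inputs, 15% dropout calls for 131 participants (132 for equal arms), and 128 leaves about 109, with omnibus power of about .79 to .795. The effect is minor. It rests on reading the 15% as a proportion of those enrolled, which is the usual meaning of a dropout rate, and on the one-way F test that reproduces 111 exactly.

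The secondary point holds only as a request for clarity. Citing reference 41 for the 15% sits awkwardly with the Discussion's account of that project and with the expectation of heavier loss at follow-ups. The documents do not show that 15% is wrong or what rate would be right. What can be said is that the 15% and the .80 should not be read as covering 6 and 12 months.

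**What to change.** Choose one of two corrections to the sentence on dropout:

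- Keep 128, and state either that it preserves 111 for dropout up to about 13%, or that power at 15% loss is about .79. This changes wording only.
- Keep the 15%, and state 131, or 132 for three equal arms of 44. This adds 3 or 4 participants.

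Then add one sentence saying that the 15% and the .80 power refer to the post-treatment comparison and are not a statement about the 6- and 12-month results. The same sentence can explain how the 15% was drawn from references 36 and 41, given what the Discussion says about the project behind reference 41. This costs nothing beyond wording and leaves the design and the analysis unchanged.

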### Recruitment

Participants will be recruited from primary care by their GPs. All patients aged 18–65 who are considered to meet eligibility criteria (based on their previous history of ED, diagnostic criteria, or clinician suspicion) will be encouraged to participate. After signing an informed consent form, the participant will have an appointment with an assessor psychologist, who will administer the measurement tools. If the participant does not meet the criteria, they will be referred back to their GP. If the participant is excluded due to a severe mental illness or a high-level disability, the GP will be advised to refer them to specialized care. Patients will receive no economic compensation for their participation in the trial.

### Allocation

The sequence will be generated before recruitment and allocation will be accomplished by a non-assessor investigator using computer software that randomly assigns participants to the three parallel clusters with a 1:1:1 ratio. Participants will receive the allocation information via email.

### Blinding

The trial will be single-blinded. Assessors and data managers will be blinded insofar as they will have no knowledge of the treatment allocation and will not be involved in the interventions. However, even though participants will be blinded during the pre-treatment evaluation, they will probably not remain blinded once allocated, since the experimental conditions are qualitatively different. For the same reason, the clinical psychologists who perform the transdiagnostic treatments will not be blinded. Since participants might consult their GPs during the intervention period, they will be asked not to share information concerning their allocation; this will ensure that the GPs are blinded.

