#### Treatment as usual (TAU)

Participants in this group will be provided with common primary care treatment by a GP in a face-to-face consultation that seldom lasts more than 10 min. TAU usually consists of pharmacological treatment, though it might also involve practical advice or even no treatment at all [51]. The first consultation will count as part of the recruitment process and, if the patient agrees to participate in the trial, no therapy will be provided until they are allocated to a group. Once in the TAU intervention, if the practitioner recommends psychological treatment (e.g., referral to specialized care), the participant would be excluded to avoid contamination between clusters. TAU does not comprise a specific number of sessions; it will end when the GP considers the patient recovered.

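### The protocol says GPs will be blinded, but GPs deliver TAU, so those treating TAU patients cannot be; elsewhere a request to participants limits disclosure but does not ensure blinding

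*Protocol article*

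**What the plan says.** The protocol article, section Blinding, calls the trial single-blinded and says that those who assess participants and those who manage the data will not know the allocation and take no part in treatment. It accepts that participants will probably not stay blinded, because the conditions differ in kind. It then adds: "For the same reason, the clinical psychologists who perform the transdiagnostic treatments will not be blinded". On GPs it notes that participants may see them during the intervention period, asks participants to keep their arm to themselves, and concludes that "this will ensure that the GPs are blinded".

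The section Treatment as usual (TAU) describes the GP's role. "Participants in this group will be provided with common primary care treatment by a GP in a face-to-face consultation". For a patient who agrees to take part, "no therapy will be provided until they are allocated to a group". TAU has no set number of sessions, and "it will end when the GP considers the patient recovered". If the practitioner recommends psychological treatment, the participant is excluded.

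Other relevant places:
- Recruitment: the patient's own GP recruits.
- Allocation: participants learn their arm by email. No notice to GPs is described.
- Collection process: measures are taken at baseline, immediately after treatment, and 6 and 12 months later.
- Anticipated limitations: GPs and clinical psychologists are named as the different personnel delivering the interventions.

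**The concern.** A clinician who gives one of the three allocated treatments, and decides when it is finished, is being described as unaware of the allocation. Those statements cannot both hold for the TAU arm.

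What is at stake is how readers interpret data that GPs influence. The Objectives and hypotheses section frames the trial's aim in terms of cost-effectiveness and cost-utility. The Cost analysis section counts medication and health-personnel costs, and TAU is said usually to be pharmacological. A reader told that GPs are blinded would take prescribing, GP consultations, length of TAU and referral as decisions made without knowledge of the arm. For TAU patients they are not.

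Timing is a second route. If the end of TAU is whatever the GP judges it to be, and the post-treatment measure follows immediately after treatment, an unblinded clinician's opinion that the patient has recovered could determine when the outcome is measured in one arm only.

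**Working it through.** The claim rests on no sample-size, power or effect-size figure, so the check is a comparison of statements.

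**1. Can a GP deliver TAU without knowing the allocation?** Before allocation the GP must hold back therapy; after allocation to TAU the GP treats.
- If the GP learns that the patient is in TAU, the Blinding section is wrong for that arm.
- If the GP does not learn it, the GP cannot know that the hold has lifted or that the TAU exclusion rule now applies. The only stated channel for the allocation is the email to the participant, who is asked not to pass it on. A TAU participant who complies would be withholding what the GP needs to begin.

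Either way, the two sections do not fit together.

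**2. Is the Blinding section consistent with itself?** It treats the psychologists as unblinded because the conditions are different in kind. GPs deliver the third condition, so the same reasoning makes them unblinded. The section does not apply it to them.

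**3. What does the request achieve in the tCBT arms?** There the GP is not the trial therapist, and the request may well lower the chance that the GP hears the allocation. It depends on participants complying, so it can limit disclosure; it cannot ensure blinding.

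**4. How many participants are concerned?** Sample size: 128 planned. Trial design: 1:1:1 allocation.
- TAU arm: 128 / 3 = 42.7, about 43 participants, or one third.
- Pairwise contrasts among three arms: 3 × 2 / 2 = 3, of which 2 involve TAU.

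These figures show how much of the trial the contradiction touches. They do not measure bias.

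**5. Which data are GP-influenced on the documents' own terms?**

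| Item | Basis in the protocol article |
|---|---|
| Prescribing and GP consultations | TAU section; Cost analysis |
| Length of TAU | TAU section (GP's judgement of recovery) |
| Referral leading to exclusion | TAU section |
| Primary outcomes | Not GP-rated: self-reported PHQ subscales (Data collection) |

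**6. Timing.** Group tCBT runs over 12–16 weeks and individual tCBT over 6 to 8 sessions; TAU has no set length. No section says that the GP's judgement fixes the assessment date, but measuring immediately after treatment, when TAU ends on that judgement, leaves it open.

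**The case against.** The strongest reply is that the sentence opens with participants who might happen to consult their GP during the intervention period, which suits tCBT patients making incidental visits better than TAU delivery. The main blinding claim covers only assessors and data managers, and the single-blind label fits that. A GP giving usual care cannot realistically be blinded, and the Anticipated limitations section already discloses that different personnel deliver the arms. On this view the sentence is merely too broad.

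Part of this stands. The narrower reading is plausible as intent, and blinding of assessors and data managers is not contradicted by anything shown here. But the sentence does not limit itself to tCBT patients, and even so limited it would promise more than a request can deliver. Nor is this a detail left to a fuller document: it is a positive statement that another section contradicts.

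The reply also rightly blocks some stronger inferences that a reader might draw:
- *GPs can work out who is in tCBT by elimination.* This is weakly supported. TAU may consist of advice or no treatment, tCBT patients may also visit their GP, and people who fail screening are referred back too. Elimination could not in any case separate the two tCBT formats.
- *Every cost item against TAU is GP-driven.* The documents do not show this. Costs also cover specialised and private care, and nothing says who certifies sick leave.
- *The primary outcomes are biased by GP knowledge.* GPs rate none of them.

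Finally, the authors say that they will consider differing durations in the analysis and try to keep timings similar between groups. That lessens the timing concern, but does not say what the TAU assessment is anchored to.

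**Conclusion.** The point holds in a limited form. The plan claims a blinding property that its own design rules out for GPs treating TAU patients (about 43 of 128), and overstates what a non-disclosure request can do in the tCBT arms. The practical effect is on interpretation of GP-influenced data in the two contrasts with TAU, and possibly on when the TAU post-treatment outcome is measured.

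The count assumes that the planned 128 are recruited and divided equally. The timing point assumes that the end of treatment in TAU means the end as judged by the GP, which the text permits but does not state. No size or direction of cost bias can be derived. The finding does not undermine the stated blinding of assessors and data managers. The correction should be made because it is cheap and changes what can be claimed.

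**What to change.** 1. Reconcile the Blinding and TAU sections: state that GPs delivering TAU are not blinded, and confine the blinding claim to assessors and data managers.
2. Keep the non-disclosure request for tCBT participants, described as a measure that limits GP knowledge of the arm rather than ensuring blinding.
3. In the report, treat prescribing, GP consultations, TAU duration and referral as open-label data when interpreting the cost contrasts with TAU.
4. Set the TAU post-treatment assessment at a time from randomisation comparable with the tCBT arms, so that the GP's view of recovery does not determine when the outcome is measured. This concerns the measurement schedule only; when TAU itself ends is a clinical matter on which no change is proposed.

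Items 1 to 3 are wording and reporting changes. Item 4 means defining an assessment time for TAU and scheduling to it; some TAU patients may then be assessed while still under treatment, which the report should say. No additional data items are needed. The price is a weaker stated blinding claim.
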